## Abstract

**Introduction::**

Chronic heart failure (CHF) is the end stage of several cardiac diseases. 50% of patients with severe CHF would survive less than 1 year, which has seriously affected patients’ survival and quality of life. The current modern therapy could improve survival and quality of life. However, a larger number of patients still suffer from repeated hospitalization, unsatisfactory efficacy, and many side effects. In China, Zhen Wu Decoction (ZWD), a classic prescription recorded in *Treatise on Febrile Diseases*, was widely used for CHF. In this study, we try to conduct a prospective, double-blinded, randomized, controlled study to evaluate the efficacy and safety of ZWD in the treatment of CHF patients in China.

**Methods::**

Patients will be randomly divided into treatment group and control group in 1:1 ratio. Guideline directed medical therapies and ZWD will be provided for patients in treatment group, while guideline directed medical therapies and ZWD-granules simulations for control group. Left ventricular ejection fraction, left ventricular end diastolic diameter, left ventricular end systolic diameter, b-type natriuretic peptide, NT-proBNP, peak VO2, VO2 maximum, exercise time, and walking distance will be recorded. The data will be analyzed by SPSS 22.0.

**Conclusions::**

The results will evaluate the efficacy and safety of ZWD in the treatment of CHF patients.

**Trial registration::**

OSF registration number: DOI 10.17605/OSF.IO/G3QNU.

## Introduction

1

Chronic heart failure (CHF) is a group of manifestations caused by either cardiac structure change or heart dysfunction resulting in impaired ventricular filling and/or ejection ability.^[1–3]^ CHF is the end stage of several cardiac diseases, include coronary artery disease, high blood pressure, valvular heart disease, and atrial fibrillation. The prevalence of CHF is increasing and it is predicted that there will be 8 million patients by the year 2030 in the USA.^[4]^ CHF patients commonly suffer from fatigue, shortness of breath, excessive tiredness, and leg swelling that limit activities in daily life. It is a potentially fatal condition, and about 35% might die in the first year after diagnosis.^[5]^ 50% of patients with severe CHF would survive less than 1 year, which has seriously affected patients’ survival and quality of life.

CHF is the leading reason of older adults for hospital admission.^[4]^ At present, treatment against CHF still focuses on the improvement of the symptoms and prevention of the progression. Common standard therapy includes angiotensin converting enzyme inhibitors (ACEI) or angiotensin receptor blocker (ARB), β-receptor blockers, aldosterone receptor antagonists, inotropic drugs, and diuretics.^[3]^ The current therapy could improve survival and quality of life. However, a larger number of patients still suffer from repeated hospitalization, unsatisfactory efficacy, and many side effects. Though cardiac resynchronization therapy has been rapidly developed, it is expensive and difficult for most patients to accept, particularly in low- and middle-income countries.

Traditional Chinese medicine could significantly improve the clinical symptoms, delay the development of the disease, and improve the long-term prognosis of CHF patients based on the common modern therapy.^[6–9]^ In China, Zhen Wu Decoction (ZWD), a classic prescription recorded in *Treatise on Febrile Diseases*, was widely used for CHF.^[10]^ However, it is still lack of high-quality and well-designed randomized, controlled trial to evaluate its efficacy and safety against CHF. Therefore, in this study, we try to conduct a prospective, double-blinded, randomized, controlled study to evaluate the efficacy and safety of ZWD in the treatment of CHF patients in China.

## Methods

2

### Patients selection

2.1

The double-blinded, randomized, controlled trial will be carried out in The People's Hospital of Dazu, and it has been approved by the Health Research Ethics Board of The People's Hospital of Dazu. The protocol conforms to SPIRIT 2013 Statement,^[11]^ and the results will be reported according to the CONSORT Statement extension for trials.^[12]^ The study was registered in open science framework (registration number: DOI 10.17605/OSF.IO/G3QNU). All patients will provide a signed written informed consent at enrollment.

Patients aged over 18 years with CHF in stable condition, New York Heart Association functional class II or III, left ventricular ejection fraction of <40% will be recruited. Patients will be excluded with the following criteria:

(1)new onset atrial fibrillation or atrial flutter;(2)complex ventricular arrhythmia at rest or presenting with exertion;(3)serious liver and kidney function damage or malignant tumor;(4)cognitive or neurological problems;(5)respiratory infection in the previous 30 days.

### Randomization and blinding

2.2

Patients will be randomly divided into treatment group and control group with a 1:1 ratio (Fig. 1). The randomization sequence will be generated by an independent statistician. The doctors, patients, and outcome assessors will be blinded to the allocation.

**Figure 1 F1:**
[figure not shown]
Flow diagram of the trial.

### Interventions

2.3

According to *Guidelines for Diagnosis and Treatment of Heart Failure in China 2018*,^[13]^ all enrolled patients will take standard guideline directed medical therapies, with a mix of ACEI or ARB, beta blockers, sacubitril/valsartan, and mineralocorticoid receptor antagonist.

In the treatment group, patients will take Chinese herbal formula ZWD, composed of *Radix Aconiti Carmichaeli* (Fuzi) 10 g, *Radix Paeoniae Alba* (Baishao) 10 g, *Rhizoma Atractylodis Macrocephalae* (Baizhu) 10 g, *Poria cocos* (Fuling) 10 g, *Rhizoma Zingiberis Recens* (Shengjiang) 10 g. The herbs will be provided as concentrate-granules and quality controlled by Beijing Tcmages Pharmaceutical CO., Ltd. The patients will be taught to dissolve the granules in 50 mL and orally take it, twice a day, for 14 days.

While in the control group, ZWD-granules simulations will be taken twice a day, for 14 days. The simulations, composed of amylum, share the same appearance, taste, dosage, and administration methods with the formula in the treatment group.

### Outcome measures

2.4

The primary outcome is the change of left ventricular ejection fraction during the treatment. The secondary outcomes are left ventricular end diastolic diameter, left ventricular end systolic diameter, b-type natriuretic peptide, NT-proBNP, peak VO2, VO2 maximum, exercise time, and walking distance. All adverse events will be also recorded.

### Sample size

2.5

In our preliminary trial, the change of left ventricular ejection fraction in the treatment group is 19%, and 10% in the control group. Taking α = 0.05, β = 0.2, 27 patients will be needed in each group. Considering a loss to follow-up of 10%, the estimated total sample size will be 60.

### Discontinue and data monitoring

2.6

The supervisor will decide for discontinuing. Case report forms (CRFs) will be used in data collection to record demographics, assessment, reasons of patient drop out. All case report forms will be preserved for at least 5 years, and the access to the original data are available from the corresponding author on reasonable requests.

### Statistical methods

2.7

The data will be analyzed by SPSS 22.0 (IBM, Chicago), with presented as mean ± standard deviation for measurement data, and percentages for count data respectively. Independent-samples *T* test, Mann–Whitney *U* test, *χ*^2^ test, or Fisher's exact test will be applied accordingly. *P* values less than .05 will be considered statistically significant.

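### For BNP and NT-proBNP, mean ± SD with baseline-unadjusted two-sample tests is a poor choice; ANCOVA on log values would gain about 7 to 21 points of power

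*Protocol article*

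**What the plan says.** Section 2.7 gives a single rule for describing continuous data: "with presented as mean ± standard deviation for measurement data". It makes no exception for skewed variables. For comparing arms on a continuous outcome it offers the independent-samples t test and the Mann–Whitney U test. The choice among the listed tests is left open: "exact test will be applied accordingly". It mentions no transformation, median, geometric mean or baseline covariate.

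Section 2.4 lists "b-type natriuretic peptide, NT-proBNP" among the secondary outcomes. It defines the primary outcome as a change in ejection fraction, but does not say whether the peptides are compared as follow-up values or as changes.

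Section 2.5 sizes the trial on ejection fraction only: "Taking α = 0.05, β = 0.2, 27 patients will be needed in each group".

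**The concern.** Two features of the rule suit these markers badly.

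- **Summary.** Natriuretic peptides are positive and can be expected to be right-skewed. The SD is then about as large as the mean or larger, and the mean lies well above the typical patient. If Mann–Whitney is used, which the plan allows, the p value comes from ranks while the reader is shown means. No effect estimate goes with the test.
- **Comparison.** Both named tests are two-sample tests without a covariate. A patient's peptide level before treatment usually predicts much of the level two weeks later, and neither test removes that variation. Analysing the change score uses baseline only by subtraction, and on the raw scale it remains skewed.

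At stake are the readability of the biomarker results and the chance of detecting a real fall in a small trial. The validity of the tests is not at stake.

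**Working it through.** **The plan's own figure.** Allowing for 10% loss, 27 / 0.9 = 30 per arm, 60 in total, which agrees with section 2.5. The 27 itself cannot be derived independently because no SD is given. With a difference of 9 (19 against 10), two-sided α 0.05 and 80% power, it follows if the SD is about 11.6 to 11.8. That calculation concerns ejection fraction, so nothing below changes it. The 27 is used here only as the number analysed per arm.

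**Assumed inputs (not in the protocol).** Lognormal marker; log-SD s = 0.8 or 1.0; correlation ρ between log baseline and log day-14 value of 0.5 to 0.8; true ratio 0.70 (30% reduction); two-sided α 0.05.

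**Summary statistic.** For a lognormal variable, mean/median = exp(s²/2) and SD/mean = √(exp(s²) − 1).
- s = 0.8: mean/median = 1.38, SD/mean = 0.95, so mean − SD is 0.05 × mean.
- s = 1.0: mean/median = 1.65, SD/mean = 1.31, so mean − SD is −0.31 × mean, impossible for a concentration.

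**Power, simulated with 4,000 trials per setting (%).** Simulation error is about 0.7 points (√(0.3 × 0.7 / 4000)), so repeat runs differ by a point or two.

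| s | ρ | t, day 14 | Mann–Whitney, day 14 | t, change | Mann–Whitney, change | log-ANCOVA | Gain over best permitted |
|---|---|---|---|---|---|---|---|
| 0.8 | 0.5 | 29 | 35 | 22 | 28 | 45–46 | 10–11 |
| 0.8 | 0.7 | 29 | 35 | 33 | 42 | 61 | 19 |
| 0.8 | 0.8 | 30 | 35 | 42 | 55 | 76 | 21 |
| 1.0 | 0.5 | 17–18 | 23 | 13 | 18–19 | 30–32 | 7–9 |
| 1.0 | 0.7 | 17 | 24 | 18 | 26 | 42 | 16 |
| 1.0 | 0.8 | 17 | 23 | 25 | 38 | 57 | 19 |

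**Check of the ANCOVA column.** The noncentrality is −ln(0.70) / (s√(1 − ρ²) × √(2/27)), with −ln(0.70) = 0.357 and √(2/27) = 0.272. The noncentral t distribution has 51 df.
- s = 1.0, ρ = 0.8: 0.357 / (0.600 × 0.272) = 2.18, power 57%.
- s = 0.8, ρ = 0.8: 0.357 / (0.480 × 0.272) = 2.73, power 76%.
- s = 1.0, ρ = 0.5: 0.357 / (0.866 × 0.272) = 1.51, power 32%.
- s = 0.8, ρ = 0.5: 0.357 / (0.693 × 0.272) = 1.89, power 46%.

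**Where the loss comes from (s = 1.0, ρ = 0.8).** A t test on log day-14 values, without adjustment, has about 26% power.
- t test on raw day-14 values: 17 to 26 is scale (9 points); 26 to 57 is baseline adjustment (31 points).
- Mann–Whitney on day-14 values: 23 to 26 is about 3 points; 26 to 57 is adjustment (31 points). Ranks of day-14 values do not change under a log transform.
- Mann–Whitney on raw change: 38 to 54 (t test on log change) is scale, because a raw change is not a log change; 54 to 57 is the remaining benefit of ANCOVA.

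**Type I error.** With no effect (s = 1.0, ρ = 0.7), the rejection rate of all the analyses was 0.038 to 0.054.

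**The case against.** The strongest reply is that the plan does list Mann–Whitney, and that leaving the choice open is ordinary shorthand for using ranks when data are not normal. A reader might infer that the plan commits BNP and NT-proBNP to a raw-scale t test and that the raw scale is what costs the power. The protocol does not support that: it assigns neither marker to either test, and for Mann–Whitney on day-14 values the raw scale costs only about 1 to 3 points. That part of the reply stands, and it places the loss for that test in the missing baseline adjustment.

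A reader might also infer that a few decompensated patients will dominate the arm means. Section 2.1 recruits patients in stable condition in NYHA class II or III, so this cannot be assumed. The effect of very high values depends on the test chosen and on skewness the protocol does not report.

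The size of the gain depends on assumptions, and a correlation of 0.8 favours ANCOVA. At 0.5 the gain falls to about 7 to 11 points. Outside the main range, at log-SD 1.2 and correlation 0.5, it is only 4 points (22% against 18%). This stands, and it is why a range is given.

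Finally, the markers are secondary, the trial claims no power for them, and a short article may leave per-variable detail to a fuller document. The first two points limit the consequence. The last does not answer the concern, because the article states a summary rule without exception and a closed list of tests; a better analysis would have to depart from both.

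**Conclusion.** The point holds as a matter of efficiency and presentation for two secondary outcomes. Mean ± SD is a poor description of a marker with a log-SD of 0.8 to 1.0 and does not match a rank test. Both permitted tests omit baseline adjustment. In the settings tabulated, ANCOVA on logs reaches about 30% to 76% power against about 23% to 55% for the best permitted test, a gain of about 7 to 21 points. The direction was the same in every setting tried; the size rests on assumed skewness, correlation and effect.

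It does not follow that any permitted test is invalid, that a stated figure is wrong, or that the trial would then be adequately powered for these markers: under most of the assumptions above, even the better analysis stays below 80%.

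**What to change.** Add to section 2.7, for BNP and NT-proBNP:

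- summarise by median (IQR) or geometric mean in place of mean ± SD;
- analyse the log day-14 value by ANCOVA with treatment arm and log baseline value as terms;
- report the between-arm ratio of geometric means with its 95% CI.

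This takes a sentence or two and settles whether follow-up value or change is analysed. It needs no data beyond a baseline and a day-14 measurement of each marker. The small downside is that the effect is read as a ratio rather than a difference, and that the analysis relies on approximate normality of the log values, which can be checked from the residuals.

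### Safety is a co-objective, but the only inference stated for adverse-event counts is a test at P<.05 with about 30 patients per arm, which cannot support a safety conclusion for uncommon events

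*Protocol article*

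**What the plan says.** The Introduction gives the aim as to "evaluate the efficacy and safety of ZWD in the treatment of CHF patients in China", and the abstract's conclusion repeats it: "The results will evaluate the efficacy and safety of ZWD in the treatment of CHF patients".

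Section 2.4 lists LVEF change as the primary outcome. The secondary outcomes are two ventricular diameters, two natriuretic peptides, two oxygen-uptake measures, exercise time and walking distance. It then adds: "All adverse events will be also recorded". It names no event type, expected rate or margin for excess harm.

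Section 2.5 bases the sample size on LVEF change only: "Taking α = 0.05, β = 0.2, 27 patients will be needed in each group", and then "Considering a loss to follow-up of 10%, the estimated total sample size will be 60".

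Section 2.7 presents measurement data as mean and standard deviation and gives "percentages for count data respectively". For inference it says "Independent-samples *T* test, Mann–Whitney *U* test, *χ*^2^ test, or Fisher's exact test will be applied accordingly", with significance declared below .05. It does not mention adverse events by name and states no interval estimate.

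**The concern.** Every primary and secondary outcome in section 2.4 is continuous. Among the listed outcomes, only adverse events give counts of patients with and without an event. Baseline characteristics aside, the chi-square and Fisher tests in section 2.7 therefore have no other stated use. The safety half of the aim rests on two percentages and a P value, at a sample size chosen for something else.

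A non-significant P value at this size is compatible both with no excess and with a large one, and the stated output does not show which. The Discussion already describes traditional Chinese medicine as having fewer side effects, so a non-significant comparison could easily be taken as confirmation when the data cannot exclude a clinically relevant excess.

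**Working it through.** **Inputs from the article.** 27 per group before loss, 10% loss, 60 in total (2.5); 1:1 allocation (2.2); threshold P<.05 (2.7).

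**Assumptions.** Two-sided tests, because sidedness is not stated. Adverse-event rates, because none are given; a range is shown.

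**The plan's own figure.** 27 / (1 − 0.10) = 30 per arm, so 60 in total, as stated. The 27 itself cannot be checked, because no standard deviation is given; this point does not depend on it.

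**Step 1: chance of missing a true excess.** For n per arm and true rates p1 and p2, all 2×2 tables are enumerated with binomial weights. The miss rate is 1 − P(test gives P<.05). Chi-square is the uncorrected Pearson test.

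| Control v ZWD (assumed) | Fisher miss, n=30 | Chi-square miss, n=30 |
|---|---|---|
| 2% v 6% | over 99% | 94% |
| 5% v 15% | 91% | 74% |
| 10% v 30% | 63% | 50% |
| 12% v 36% | 51% | 40% |
| 15% v 45% | 36% | 26% |
| 20% v 60% | 15% | 10% |
| 10% v 20% | 91% | 81% |
| 20% v 40% | 70% | 61% |

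The first six rows are triplings and the last two are doublings. A tripling is missed more often than not only if the control rate is below about 12% (Fisher) or about 10% (chi-square). With 27 evaluable per arm the Fisher miss is 93% for 5% v 15% and 69% for 10% v 30%.

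**Step 2: what separates significant from non-significant.** With no events on control, two-sided Fisher P = 2 × C(30,k) / C(60,k) for k events on ZWD.
- k = 5: 2 × 142,506 / 5,461,512 = 0.052.
- k = 6: 2 × 593,775 / 50,063,860 = 0.024.

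So five events against none is non-significant by Fisher's test.

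**Step 3: what the data leave open, whatever the true rates.** The Newcombe 95% interval for the risk difference is built from the Wilson limits (l, u) of each arm:
- upper limit = (pZ − pC) + √[(uZ − pZ)² + (pC − lC)²]
- lower limit = (pZ − pC) − √[(pZ − lZ)² + (uC − pC)²]

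Results at 30 per arm:
- 0/30 v 0/30: Wilson limits 0 and 3.84 / 33.84 = 0.114. Upper limit = √(0.114² + 0²) = 0.114, or +11.4 points.
- 3/30 v 3/30: Wilson limits 0.035 and 0.256. Upper limit = √(0.156² + 0.065²) = 0.169, or +16.9 points.
- ZWD 9/30 v control 3/30: Wilson limits on ZWD are 0.167 and 0.479. The difference is 20 points, interval −0.5 to +39.0. Fisher P = 0.104; chi-square = 60 × (9×27 − 3×21)² / (12×48×30×30) = 3.75, P = 0.053.
- ZWD 12/30 v control 4/30: Fisher P = 0.039, chi-square P = 0.020, so a tripling at that level is declared significant.

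For one arm alone, zero events in 30 gives a one-sided 95% upper limit of 1 − 0.05^(1/30) = 9.5%.

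**The case against.** The strongest reply is that the article contains no wrong statement here. Section 2.7 lists generic tests, does not assign them to adverse events, and nowhere says that non-significance shows safety. Adverse-event tables and interval methods are commonly left to a full protocol or analysis plan, and neither is shown. Percentages are reported too, and with arm sizes known a reader could compute the risk difference and its interval. Low power for uncommon harms is true of almost any 60-patient, 14-day trial.

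Much of this stands. A reader might infer that the plan equates P>.05 with safety; it does not say so. A reader might infer that the test is the only thing reported on counts; percentages are reported as well. A reader might infer that a tripled adverse-event rate would usually go undetected. That holds only for control rates below about 10% to 12%, reverses above them (20% v 60% is missed 15% of the time by Fisher, 10% by chi-square), and depends on a rate the article does not give. The choice of test also matters: if the usual expected-count rule of 5 is meant (an assumption), chi-square would often be the test used at 10% v 30%, where the expected count is about 6, and its miss rate there is 50%.

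What does not stand is that this is merely a missing detail. The article states an inferential method, and adverse events are the only listed outcome that calls for the count tests in it. At the stated size that method cannot answer the safety half of the aim for uncommon events. Percentages are presentation and carry no uncertainty; that a reader could derive the interval is a reason for the plan to report it.

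**Conclusion.** The point holds as an inexpensive improvement, not as a proven error. Percentages with a chi-square or Fisher P value, at about 30 per arm in a trial sized on LVEF, cannot support a safety conclusion for uncommon events.

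The size of the power problem depends on assumed event rates and two-sided testing: severe at a 5% control rate, roughly even at 10% to 12%, and mostly gone for triplings from 15% upward, although the doublings examined are still missed 61% to 91% of the time. The interval result needs no assumed rate: even identical low counts in the two arms leave a double-digit excess in percentage points unexcluded. The documents do not support a claim that the trial would reassure almost regardless of the truth.

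**What to change.** In section 2.7, say that adverse events will be reported as the number and percentage of patients per arm, with the risk difference and its 95% confidence interval (Newcombe or exact). Say that any safety statement will rest on the upper limit of that interval, and that P>.05 will not be taken as evidence of safety. In the aim and the abstract's conclusion, describe the safety assessment as preliminary.

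The cost is a few sentences and one extra column in the adverse-event table, with no added patients or visits. The downside is a more modest safety claim.

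### The tests named for the LVEF change use baseline LVEF only by subtraction; naming ANCOVA as the primary analysis would gain precision at no cost in patients or data

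*Protocol article*

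**What the plan says.** Section 2.4 (Outcome measures) of the protocol article fixes the endpoint: "The primary outcome is the change of left ventricular ejection fraction during the treatment". Section 2.1 (Patients selection) makes LVEF an entry criterion: "left ventricular ejection fraction of <40% will be recruited".

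Section 2.7 (Statistical methods) gives the tests in one sentence: "Independent-samples *T* test, Mann–Whitney *U* test, *χ*^2^ test, or Fisher's exact test will be applied accordingly". For a continuous outcome such as LVEF change, that leaves the first two: "Independent-samples *T* test, Mann–Whitney *U* test". Neither takes a covariate, and no regression or covariance model is named.

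Section 2.5 (Sample size) reports from a preliminary trial that "the change of left ventricular ejection fraction in the treatment group is 19%, and 10% in the control group". It then says: "Taking α = 0.05, β = 0.2, 27 patients will be needed in each group". It gives no standard deviation and no baseline to follow-up correlation.

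**The concern.** Subtracting baseline fixes its coefficient at 1. In patients chosen for a low LVEF, the slope of follow-up on baseline will usually be below 1, because some of the low entry values are measurement error or temporary dips. Change is then negatively related to baseline. That relation stays in the error term of a t test on change, and any chance baseline difference between two arms of about 27 to 30 carries into the observed difference in change. ANCOVA estimates the slope instead of assuming it.

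At stake is the precision of the primary comparison in a trial planned at only 80% power with about 54 evaluable patients. The covariate that would recover the lost precision is already being collected.

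**Working it through.** **Inputs from the protocol article**

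- Difference in LVEF change: 19 − 10 = 9 (Sample size). The text does not say whether this is in absolute points or relative per cent; absolute points are assumed here.
- α = 0.05, power 0.80, 27 per arm (Sample size). Two-sided testing is assumed, since sidedness is not stated.
- 1:1 allocation (Randomization and blinding).

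**Inputs not in the document**

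- r, the correlation of baseline with end-of-treatment LVEF: shown over a range.
- The SDs at baseline (σx) and follow-up (σy): taken as equal first, then as unequal.

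**1. The plan's own figure.** The 27 per arm cannot be reproduced directly because no SD is given. Solving backwards with the normal approximation:

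SD of change = 9 × √(27/2) / (1.960 + 0.842) ≈ 11.8

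So 27 per arm fits a two-sided comparison of means if the SD of change is about 11.8 (11.6 with the t distribution). Reading 19% and 10% as proportions would need 240 per arm, so the calculation is evidently for means. The dropout step reproduces: 54 / 0.9 = 60.

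**2. Variance of the two analyses, equal SDs (σx = σy = σ)**

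- Change score: 2σ²(1 − r)
- ANCOVA: σ²(1 − r²)
- Ratio: (1 − r²) / [2(1 − r)] = (1 + r)/2

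**3. Power at 27 per arm.** The change-score test is taken to have exactly 80% power, so its expected z is 1.960 + 0.842 = 2.802. For ANCOVA the expected z is 2.802 / √ratio. For example, at r = 0.5 it is 2.802 / √0.75 = 3.235, and 3.235 − 1.960 = 1.275 gives power 0.90.

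| r | Variance ratio | ANCOVA power at 27 per arm | Per-arm n for 80% power |
|---|---|---|---|
| 0.3 | 0.65 | 0.93 | 18 |
| 0.5 | 0.75 | 0.90 | 21 |
| 0.7 | 0.85 | 0.86 | 23 |
| 0.8 | 0.90 | 0.84 | 25 |
| 0.9 | 0.95 | 0.82 | 26 |

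The power column does not depend on the back-solved SD, only on the starting 80% and on r. ANCOVA costs one residual degree of freedom (51 instead of 52 with 54 patients), which is negligible.

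**4. Unequal SDs.** The entry limit truncates LVEF at baseline but not at follow-up, so σx may be below σy. In general:

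- Change score: σx² + σy² − 2rσxσy
- ANCOVA: σy²(1 − r²)
- Difference: (σx − rσy)², which is never negative and is zero when rσy = σx, that is, when the slope is 1

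Two illustrations, both assumptions:

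- *σx = 0.75σy.* At r = 0.5 the change-score variance is 0.5625 + 1 − 0.75 = 0.8125 (in units of σy²) and the ANCOVA variance is 0.75, a reduction of about 8%. At r = 0.7 they are 0.5125 and 0.51, a reduction of about 0.5%.
- *Selection halves the baseline variance, with the slope and residual variance unchanged.* Take the unselected variances as 1. At an unselected r of 0.5 the change-score variance is 0.5² × 0.5 + 0.75 = 0.875, and the ratio is 0.75 / 0.875 = 0.86 (power 0.86). At 0.7 it is 0.3² × 0.5 + 0.51 = 0.555, and the ratio is 0.51 / 0.555 = 0.92 (power 0.83).

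So for r of 0.5 and 0.7, the equal-variance reductions of 25% and 15% fall to about 14% and 8% in one illustration, and to about 8% and 0.5% in the other.

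**The case against.** The strongest reply is that nothing here is wrong. A two-sample test on change in a 1:1 randomised trial is unbiased and controls type I error. Regression to the mean acts on both arms alike, and chance baseline imbalance is already reflected in the standard error. The article condenses a fuller plan in which a covariate model might appear. The size of the gain rests on an r that the document does not give and on an equal-variance assumption that the LVEF entry limit itself makes doubtful.

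Most of this stands, and it limits the point to efficiency. It does not remove it. Section 2.7 is not silent on method: it names the tests, and those it names for continuous outcomes are all unadjusted. Improving a stated method is different from asking for detail held elsewhere. The variance algebra also shows that, apart from one degree of freedom, ANCOVA cannot be less precise than the change score under this model.

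A reader might infer more than the text supports:

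- *That baseline is ignored.* It is not; the endpoint is a change, so baseline enters by subtraction.
- *That the test will be picked after seeing the results, inflating type I error.* Section 2.7 says only that tests are applied as appropriate, which ordinarily means by data type and distribution. Simulating the practice of always reporting the smaller of the t and Mann–Whitney p values gives an error of about 5.8% with normal data and 6.6% with lognormal data. That models selective reporting, which the plan does not propose, and the rule for choosing may stand in an analysis plan that is not shown.
- *That the secondary outcomes will be compared on end values alone.* Section 2.4 lists them by name without stating the form in which they will be analysed.

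**Conclusion.** The point holds as one of precision. The named analysis of the primary outcome is valid but uses baseline LVEF less efficiently than it could. With equal variances and a change-score test at 80% power, the gain from ANCOVA runs from about 2 percentage points of power at r = 0.9 to about 13 at r = 0.3. It is smaller, possibly near zero, if the entry criterion leaves baseline LVEF less variable than follow-up LVEF. The document gives neither r nor any SD, so the gain can be shown only as a range. The figures also assume two-sided testing and change in absolute points. Neither bias nor an inflated type I error is shown.

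**What to change.** In section 2.7, name one primary analysis: ANCOVA of end-of-treatment LVEF on treatment group with baseline LVEF as covariate, reporting the adjusted mean difference with its 95% confidence interval and a two-sided p value. Using the change in LVEF as the response gives the same adjusted treatment difference, so the endpoint in section 2.4 need not be redefined. Apply the same model to the continuous secondary outcomes, each with its own baseline, and keep Mann–Whitney only as a sensitivity analysis.

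For LVEF, the cost is about two sentences of text. No further data or patients are needed, and the planned software can fit the model. The sample size can stay as it is, with any gain taken as extra power.
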